**Methods/Design:**

Our implementation strategy uses three models of organizational change: the Program Planning Model to promote acceptance and sustainability, the NIATx quality improvement model to create a welcoming environment for change, and Rogers’s diffusion of innovations research, which facilitates adaptations of innovations to maximize their adoption potential. We will implement Seva and conduct an intensive, mixed-methods assessment at three diverse Federally Qualified Healthcare Centers in the United States. Our non-concurrent multiple-baseline design includes three periods — pretest (ending in four months of implementation preparation), active Seva implementation, and maintenance — with implementation staggered at six-month intervals across sites. The first site will serve as a pilot clinic. We will track the timing of intervention elements and assess study outcomes within each dimension of the Reach, Effectiveness, Adoption, Implementation, and Maintenance framework, including effects on clinicians, patients, and practices. Our mixed-methods approach will include quantitative (*e.g*., interrupted time-series analysis of treatment attendance, with clinics as the unit of analysis) and qualitative (*e.g*., staff interviews regarding adaptations to implementation protocol) methods, and assessment of implementation costs.

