### Timeline

Data will be collected from each FQHC for 48 months using a combination of data sources, including electronic health records, staff surveys/interviews, and patient surveys/interviews. We are collecting staff survey data every 6 months for 36 months, patient survey data every 6 months for 18 months, and aggregated EHR data for 48 months to cover the full time frame from the beginning of the pretest period at FQHC 1 to the end of the posttest period at the FQHC 3. Figure 
2 shows more information about the project timeline. Retrospective data collection will take place during the pretest period, using aggregated patient data from clinics’ electronic health records. During the pretest period, sites will also seek to identify potential patient candidates for recruitment. Full-scale implementation occurs during the subsequent 12 months, during which the sites receive coaching and actively recruit patients to use Seva. The sites will continue to be monitored during a post-test/sustainability period. During this period, sites may continue recruiting patients to use Seva, but without grant funding for phone/internet support or organizational coaching.

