### Study design

Our study uses a non-concurrent multiple-baseline design in which the start of the intervention period is staggered at the three sites by six months. The multiple-baseline design provides the intervention to all participants, but isolates the independent variable by introducing the intervention at specified points. Using the clinic as the unit of analysis, this single-subject approach will closely track the timing of intervention elements and repeatedly measure outcomes at the organizational level, including aggregated effects on clinicians, patients and practices. After pilot testing Seva at the first FQHC and improving Seva and the overall implementation strategy, we will introduce Seva at the second FQHC and then, six months later, at the third FQHC. Each FQHC acts as its own pretest control. During the 48-month data collection period, core organizational indicators will be measured via a staff survey (administered every 6 months) and the clinics’ electronic health records (aggregated across patients). While the non-concurrent multiple-baseline design may not provide as strong a basis for causal inference as a large RCT, we believe it is the appropriate design for evaluating the organizational impact of a system that has already been shown effective in RCTs of patients
[45]. We will also collect a set of standard CHESS/TES measures via a patient survey for comparison to previous studies that tested these technologies in RCTs, and to conduct exploratory analyses. The patient survey also provides supplemental clinical information not routinely collected in the clinics (*e.g*., addiction severity, quality of life, etc.).

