### Analysis

We will use a mixed-method approach, using both quantitative and qualitative methods, to assess our implementation model. Our analysis follows guidelines for mixed-methods research promulgated by the NIH Office of Behavioral and Social Sciences Research
[51]. Because this is a study of the organizational impact of Seva, there will be no single-patient analyses; all analyses will be aggregated across patients.

Analysis of quantitative outcomes will proceed on three fronts:

1. Descriptive statistics will be used to assess relevant Reach outcomes.

2. Interrupted time series analysis will compare selected Effectiveness and Maintenance outcomes within a clinic before and after implementation. We will assess whether our implementation model promotes the successful installation and use of Seva using linear regression models, with each analysis having two time-series segments representing means and slopes before and after implementation. A test of the regression coefficient for implementation (a dichotomous variable indicating whether the time point occurred before or after implementation) will allow us to examine differences in the mean change at implementation. Differences in slope from pre- to post-implementation will be tested using the coefficient for the implementation x month interaction, where ‘month’ is a continuous variable indicating the month of measurement. Weighted least squares analysis will be used to account for potential differences in the number of patients or staff reporting outcomes within each clinic across time. Given the limited degrees of freedom, no covariates will be included in the models.

3. Drawing from conventional approaches to single-subject analysis, we will also compare selected RE-AIM outcomes within and across the clinics using data visualization
[52] to determine whether the shifts between intervention phases of the study generated shifts in the level, trend, and variability of performance
[53]. This will allow us to evaluate the immediacy, consistency and magnitude of the observed effects
[52].

The qualitative analysis is designed to:

1. Understand the environments in which Seva is implemented, how Seva was tailored to fit each environment, and the processes used to tailor Seva. Focus groups and observational and interview data will help us understand the environment and the processes used to tailor Seva.

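### The segmented regression of each clinic's monthly EHR series makes no allowance for serial correlation, so positive month-to-month correlation would make its level and slope tests too liberal

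*Protocol article*

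**What the plan says.** In the protocol article, item 2 of the quantitative list under Analysis sets out the interrupted time series method. Outcomes are compared within a clinic before and after implementation "using linear regression models, with each analysis having two time-series segments representing means and slopes before and after implementation". Two coefficients are tested: the implementation indicator (change in level) and its interaction with month (change in slope), where month "is a continuous variable indicating the month of measurement". The estimator and the purpose of its weights are then given: "Weighted least squares analysis will be used to account for potential differences in the number of patients or staff reporting outcomes within each clinic". Nothing else enters the model: "Given the limited degrees of freedom, no covariates will be included in the models".

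The Abstract gives as its example "interrupted time-series analysis of treatment attendance, with clinics as the unit of analysis", and Study design says the approach will "repeatedly measure outcomes at the organizational level". Timeline gives the length of the EHR series: "aggregated EHR data for 48 months to cover the full time frame from the beginning of the pretest period at FQHC 1". Staff surveys are half-yearly for 36 months; patient surveys are half-yearly for 18 months.

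No section mentions autocorrelation, an error model that allows for it, a residual check or robust standard errors.

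**The concern.** Each test rests on one series from one clinic, so the scatter of the monthly points about the two fitted lines is the only source of the standard error. Weighted least squares treats those points as independent once unequal variance has been allowed for. Successive monthly aggregates from one clinic share staff, workflow and, for some measures, patients. Positive correlation is therefore the natural expectation, although the article does not document it. If it is present, ordinary drift within a clinic looks more precise than it is.

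These two coefficients carry the only formal before/after tests that the Analysis section describes. Item 1 of the list is descriptive and item 3 is visual. The Economic analysis section also relies on before/after change in utilization.

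**Working it through.** The article states no error rate or power, so there is no figure to reproduce. The check is how the stated method behaves when nothing changes at implementation.

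**Inputs from the article.** Two-segment model with 4 parameters (Analysis); monthly time unit (Analysis); 48 months of aggregated EHR data (Timeline), hence 48 − 4 = 44 residual degrees of freedom; clinic as unit (Abstract, Study design).

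**Assumptions, because the article gives no value.** AR(1) normal errors with lag-1 correlation ρ; two-sided 5% t test; go-live after month 12, 18, 24 or 30, with month 6 as a further case (the timeline figure is not shown).

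**Formula.** Let X be the design matrix and R the error correlation matrix, with entries ρ^|i−j|. Up to the error variance:
- true variance of the estimates: (X′X)⁻¹ X′RX (X′X)⁻¹
- variance that least squares reports: s²(X′X)⁻¹, where E(s²) = tr(MR)/44 and M = I − X(X′X)⁻¹X′.

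The square root of reported over true variance is the factor by which the standard error is understated.

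**Approximate check by hand, go-live after month 18.** The critical value is t(0.975, 44) = 2.015. If the standard error is understated by factor f, the true rate is about P(|t₄₄| > 2.015 f).
- ρ = 0.2: f = 0.83 (level), 0.81 (slope). 2.015 × 0.83 = 1.67 gives 10.1%; 2.015 × 0.81 = 1.63 gives 11.0%.
- ρ = 0.4: f = 0.68, 0.65. 2.015 × 0.68 = 1.37 gives 17.7%; 2.015 × 0.65 = 1.31 gives 19.7%.

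**Simulation of the planned fit** (40,000 null series per setting, equal weights; level / slope):

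| Go-live after month | ρ = 0 | ρ = 0.2 | ρ = 0.4 |
|---|---|---|---|
| 12 | 5.2% / 4.9% | 9.5% / 9.8% | 16.1% / 16.8% |
| 18 | 5.0% / 5.0% | 10.0% / 10.7% | 17.4% / 19.4% |
| 24 | 5.0% / 5.2% | 10.2% / 10.8% | 18.1% / 20.5% |
| 30 | 5.1% / 4.9% | 9.8% / 10.5% | 18.0% / 19.7% |

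The ρ = 0 column confirms that the set-up is sound. With go-live after month 6 the rates are about 8% at ρ = 0.2 and 11% at ρ = 0.4. The chance that at least one of the two tests is falsely significant at ρ = 0.4 is 26-35% for go-live after month 12 to 30, against 8-10% at ρ = 0.

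**Sensitivity.**
- Unequal weights (30 to 100 reporters) at ρ = 0.4, go-live after month 18: 18.0% / 19.1%, so weighting does not help.
- AR(1) at 0.4 plus independent noise of equal variance: about 11-12%.
- ρ = −0.2: about 2%.
- Seven half-yearly points, as in the staff survey: 4-12% for ρ up to 0.5.

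**Candidate remedies, 48 months** (level / slope where two figures are given):
- AR(1) generalised least squares by REML: about 6-8% at ρ = 0.2 to 0.4, go-live after month 12 to 30.
- Prais-Winsten with estimated ρ, go-live after month 18: 9.2% / 10.1% at ρ = 0.3; 11.4% / 12.4% at ρ = 0.5.
- Newey-West, lag 3, go-live after month 18: 18.2% / 20.4% at ρ = 0.3, against 13.6% / 14.5% for plain least squares.

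**The case against.** The strongest reply has four parts.

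**The article is a condensed text.** It nowhere says that errors are independent, and an unseen analysis plan might add an error model. A reader might infer that independence is stated; it is not. It is what the named estimator assumes when its weights address only numbers reporting. But the article does fix the estimator, the tests, the purpose of the weights and the exclusion of covariates, so this is a stated method and not an omitted detail.

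**The size depends on unknowns.** Autocorrelation, alpha and go-live month are all assumed here. Some EHR measures, such as the number screened for HIV, need not recur in the same people, and sampling noise in small clinics dilutes the correlation. This stands: the rates are conditional, and could be lower than those tabulated.

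**The scope is limited.** A reader might carry the rates over to every outcome. The article does not support that. Only the EHR aggregates run for 48 months. Substance use, the primary effectiveness outcome, comes from weekly Seva reports and patient surveys at 0, 6, 12 and 18 months (Table 1). Staff data are half-yearly.

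**The tests do not carry the conclusion alone.** A reader might infer that drift would be declared an implementation effect. The article states no alpha or decision rule, concedes weaker causal inference than a large randomised trial, labels utilization analyses exploratory and adds visual comparison across staggered clinics. This moderates the consequence, but none of it corrects the standard errors.

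**Conclusion.** The point holds for the monthly EHR series. As written, the level and slope tests have standard errors that are too small whenever months are positively correlated. Under AR(1) errors, a two-sided 5% level and go-live after month 12 to 30, the false-positive rate is about two to four times nominal for correlations of 0.2 to 0.4. It is nearer 8% and 11% if go-live falls after month 6.

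This should be fixed, but it does not undermine the study as a whole. The size rests on assumed values, the primary effectiveness outcome lies outside the calculation, and the article does not rest its conclusions on these tests alone.

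**What to change.** Amend the weighted-least-squares sentence under Analysis so that monthly series are fitted by generalised least squares with AR(1) errors estimated by REML. Keep the weights for numbers reporting, apply a small-sample degrees-of-freedom correction, and report the estimated autocorrelation with each result. Newey-West intervals should not be used at this series length, where they did worse than plain least squares in most settings examined. Prais-Winsten without a small-sample correction should not be used either.

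The cost is a sentence or two of analysis text, slightly more analysis work and wider intervals. No new data are needed. According to Trial status, the pilot clinic was only entering its pre-implementation period at submission, so the change could be made before any post-implementation results were seen.

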## Background

### Context

This paper describes the protocol for a study on implementing mobile-health technology in primary care. The study is funded by the United States’ National Institute on Drug Abuse as part of a request for proposals aimed at integrating addiction treatment into primary care*.* Although numerous smartphone applications exist that address many health problems, primary care clinicians do not commonly incorporate mobile technology into patient care
[1]. One reason is that very few smartphone applications have been proven in rigorous trials of effectiveness. Even if an application does have a reliable evidence base, it must still demonstrate its value to various stakeholders if it is to be widely used. Patients must see value in the application or they are likely to stop using it. Clinicians must find it useful to incorporate it in day-to-day clinical management. Finally, clinic administrators must find that the application works both clinically and financially to support its use by patients and staff.

Our study focuses on Federally Qualified Health Centers (FQHCs) in the United States, community-based organizations that provide primary care and preventive health services to patients regardless of their ability to pay. FQHCs (and U.S. primary-care practices in general) are increasingly being encouraged by healthcare reform to integrate treatment for addiction and behavioral health into their practices. HIV testing and prevention efforts are particularly important for the health of men and women who use illicit drugs because they are at higher risk than the general population for acquiring HIV
[2,3]. But transforming primary care to address addiction and HIV will likely add to the work of clinicians, many of whom already feel overburdened. Previous attempts to integrate addiction treatment into primary care have largely relied on labor-intensive solutions (*e.g*., adding more staff or having staff do tasks differently), with mixed results
[4].

Our premise is that mobile health technology holds great promise for FQHCs to reach this complex patient population. More than two-thirds of individuals with substance use disorders (SUDs) have had contact with a primary-care provider in the previous six months
[5], for reasons that may or may not relate to their SUD
[6]. But primary-care providers frequently do not screen for or treat SUDs, even though recovery support can be effectively administered in primary care

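### The degrees-of-freedom reason for excluding covariates does not fit the 48-month EHR series, where seasonality or an abrupt shared change can be read as an effect of Seva

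*Protocol article*

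**What the plan says.** Item 2 of the quantitative plan (Protocol article, Analysis) is an interrupted time series regression that will "compare selected Effectiveness and Maintenance outcomes within a clinic before and after implementation". It has two segments, each with its own mean and slope. The tests are on the implementation indicator and on its interaction with a continuous month variable. Weighted least squares handles varying numbers of reporters. The item ends: "Given the limited degrees of freedom, no covariates will be included in the models". Item 3 compares clinics with one another, by data visualization.

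On data density, the Timeline section says "Data will be collected from each FQHC for 48 months using a combination of data sources". Staff surveys come every 6 months for 36 months and patient surveys every 6 months for 18 months. The EHR extract is "aggregated EHR data for 48 months to cover the full time frame from the beginning of the pretest period at FQHC 1" and runs to the end of the third clinic's posttest, so it spans one calendar window common to all clinics. Under Study design, "the start of the intervention period is staggered at the three sites by six months", and each clinic serves as its own pretest control. The Context section notes that these centers "are increasingly being encouraged by healthcare reform to integrate treatment for addiction and behavioral health into their practices".

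**The concern.** One exclusion rule, with one reason, is applied to series of very different length. Where the series is long the reason does not hold, and the exclusion has a price: the model has no term for month of the year and none for events that affect all clinics at once. Attendance, utilization and screening counts could plausibly vary over the year.

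At stake are the EHR outcomes in the effectiveness domain: treatment attendance (the Abstract's own example of this analysis), HIV screening and healthcare utilization. The Economic analysis section also relies on the design to judge whether reduced utilization offsets implementation cost. A seasonal peak or a shared shift near go-live could be reported as a change brought about by Seva, or could hide one.

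**Working it through.** The plan states no power, alpha or sample-size figure, so there is nothing to reproduce. The check counts degrees of freedom, then applies the plan's model to series with no Seva effect.

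**Inputs from the article:** 48 months of EHR data per clinic, four regression parameters, six-month stagger, four-month preparation before each start, and the survey schedules above.

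**Assumptions:** monthly EHR points (inferred from the month term and from Table 1 listing these data as continuous); independent errors with SD 1; equal weights; two-sided 5% tests; post-implementation months counted from go-live. Pretest length is not in the available text (the timeline figure is not shown), so a range is used.

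**Residual degrees of freedom** = time points − parameters:
- EHR, per clinic: 48 − 4 = 44; with a sine/cosine pair, 48 − 6 = 42.
- Staff survey: 7 waves (0 to 36 months) − 4 = 3.
- Patient survey: 4 waves − 4 = 0.

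**Model**, with p pre-implementation months: y(t) = b0 + b1·t + b2·I(t>p) + b3·I(t>p)·(t−p−1).

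**Steady shared trend.** Adding a linear drift gives zero bias in b2 and b3, because b1 absorbs it.

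**Annual cycle.** Let c(t) = A·sin(2πt/12 + φ). The false level change is the b2 element of (X'X)⁻¹X'c. With A = 1 SD:

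| p | Largest false level change (SD) | Level-test false positives, averaged over φ | Level SE without → with sine/cosine pair |
|---|---|---|---|
| 6 | 1.60 | 11% | 0.98 → 1.04 |
| 12 | 1.37 | 16% | 0.70 → 0.76 |
| 18 | 0.36 | 3% | 0.61 → 0.61 |
| 24 | 0.97 | 12% | 0.58 → 0.62 |

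With p = 12, the averaged rate falls to about 9% at A = 0.5 SD and 6% at A = 0.25 SD. Adding the sine/cosine pair returns it to about 5% at every p. The largest SE increase is 0.764/0.697 = 1.10.

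**Abrupt shared change.** A 1-SD step in a clinic's own start month is returned as a level change of exactly 1.00 SD. With 12 pre-months at the first clinic, it produces 29%, 36% and 40% false positives on the level test at clinics 1, 2 and 3. A sine/cosine pair does not remove this.

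**Comparison with a clinic not yet started.** Take the difference between the two clinics' series, using only months before the control clinic's own start. The level SE is √(2·[(X'X)⁻¹] for b2) on the shortened series. For a first-clinic pretest of 6 to 18 months, its ratio to the within-clinic SE is:
- clinic 1 against 2: 1.7 to 2.0
- clinic 2 against 3: 1.9 to 2.05
- clinic 1 against 3: 1.6 to 1.7

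The next clinic in line enters preparation 6 − 4 = 2 months after the previous go-live. Excluding its preparation therefore leaves two post-go-live months, and the SE grows further.

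**The case against.** Four points on the other side have force.

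- **The trend is already modelled.** A reader might infer that the healthcare reform described under Context will be credited to Seva. The article describes growing encouragement, which the slope largely absorbs. It documents no abrupt reform step at any go-live and no seasonal pattern in any outcome. So the claim is that such changes can be read as an effect, not that they will be.
- **The maxima are worst-phase values** at a large amplitude. Averaged over phase the inflation is moderate, and with 18 pre-months it disappears.
- **The clinics are not clean controls.** A reader might infer that the staggered clinics supply a ready-made controlled analysis. They were chosen for diversity, the next in line is soon in active preparation, and Seva and the strategy are to be improved after the pilot. This rules out making the comparison the main analysis.
- **The scope is limited.** Substance use, the primary effectiveness outcome, comes from Seva and the patient survey, not the EHR. Limitations calls the utilization analyses exploratory, and Study design concedes weaker causal inference than a large randomized trial.

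Two replies stand. The visual comparison across clinics in item 3 may reveal a shared shift, but it neither corrects nor tests the reported coefficients. And the article does not merely leave covariates to a later plan: it rules them out for a reason that fails for these series.

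**Conclusion.** The concern holds for EHR outcomes analysed monthly. With 44 residual degrees of freedom per clinic, limited degrees of freedom is no reason to omit a seasonal term; for the surveys, with 3 and 0, it is. An annual cycle of 1 SD can produce a false level change of about 0.4 to 1.6 SD depending on pretest length. With 12 pre-months the phase-averaged false-positive rate is about 16%, or 6% to 9% for smaller cycles. These sizes rest on independent errors and on assumed amplitudes and pretest lengths. The documents do not support saying that all shared calendar change is credited to Seva, or that the primary effectiveness outcome is affected through the EHR.

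**What to change.** 1. Limit the no-covariates rule, and its reason, to survey outcomes.
2. For monthly EHR outcomes, add one annual sine/cosine pair to the within-clinic model. This leaves 42 degrees of freedom and raises the level SE by at most about 10%.
3. As a sensitivity analysis only, report beside the within-clinic estimate a comparison with clinics not yet implementing. Use control months before that clinic's own start, and flag or exclude its four-month preparation period.
4. State that comparison's downsides: a level SE about 1.6 to 2.0 times larger (more if preparation months are dropped), the assumption that deliberately diverse clinics share the same shocks, and no untreated clinic at the third go-live.

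The cost is analysis work only, with no new data, because the EHR extract already covers the common window.

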### Settings for implementation

We worked with the National Association of Community Health Centers to identify a set of FQHCs with established electronic health records. We focused on FQHCs with electronic health records because healthcare reform has been pushing FQHCs in this direction, and we believe it will be important to understand how Seva relates to existing clinic technology. From the pool of FQHCs that met these criteria, we selected an FQHC affiliated with the University of Wisconsin as our first implementation site; as a second site, a relatively small, rural, freestanding FQHC with integrated behavioral health services (including addiction treatment); and as a third site, an urban FQHC that serves a largely minority population. In selecting sites, we strove to maximize diversity in both patient populations and organizational structures to better understand how environment affects implementation. We included only three FQHCs in order to conduct an intensive, mixed-methods assessment at each clinic, which we believe will be more informative for the ultimate purpose of dissemination than randomizing a larger sample of organizations and studying implementation at a surface level.

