#### Reach

In assessing reach, we will determine how many patients are eligible to use Seva within each clinic, how many are excluded, how many are invited to participate, and how many enroll in the study. We will also study how quickly patients are enrolled after the beginning of the enrollment period. We will assess how representative Seva enrollees are of the target population (substance using patients within each clinic) by comparing users to the target population on key clinical characteristics (*e.g*., treatment attendance, healthcare utilization). Qualitative assessment will supplement our data collection on reach. Our goal is to understand how clinicians perceive or anticipate which patients may benefit most from the system, because — for budget reasons — not all patients can have Seva, either in this study or in a broader dissemination. (In this study, we can offer Seva to a maximum of 100 patients per clinic.) For example, clinicians may select patients to enroll who they think will be strong models for other patients, or patients who have had many relapses and may benefit from a different treatment approach. As an implementation-focused study, we strive not for random selection but instead encourage clinicians to enroll patients for whom they believe Seva will be most helpful.

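### A fall in the scatter of Seva-user series from the active phase to maintenance can come from enrolment alone, and the visual analysis makes no allowance for the number of patients behind each point

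*Protocol article*

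**What the plan says.** The Analysis section of the protocol article states that "all analyses will be aggregated across patients". Two of its quantitative items bear on this point.

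- **Item 2 (interrupted time series).** "Weighted least squares analysis will be used to account for potential differences in the number of patients or staff reporting outcomes" within each clinic over time. The plan thus expects the count behind a time point to vary and handles this in the regression.
- **Item 3 (visual analysis).** Selected RE-AIM outcomes are compared within and across clinics "to determine whether the shifts between intervention phases of the study generated shifts in the level, trend, and variability of performance". The next sentence gives the purpose: "This will allow us to evaluate the immediacy, consistency and magnitude of the observed effects". No threshold is set for a variability shift, and the counts are not mentioned.

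On what drives the counts, the Timeline section says: "Full-scale implementation occurs during the subsequent 12 months, during which the sites receive coaching and actively recruit patients to use Seva". The Reach section adds that "we can offer Seva to a maximum of 100 patients per clinic". In the post-test period sites may go on recruiting, without grant support for phones. Table 1 gives Seva as the weekly source for substance use, which the Effectiveness section names as the primary effectiveness outcome. The other source for that outcome is the patient survey at 0, 6, 12 and 18 months.

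**The concern.** The scatter of an aggregate has two parts: real month-to-month movement, and sampling error that falls as the number of patients rises. Unequal numbers do not bias the expected level of a series, but they change its expected scatter directly. Item 2 allows for the numbers when estimating coefficients. Item 3 does not, although variability is the one feature it reads that depends on them directly.

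Seva check-ins and log data start at enrolment, so these series have no pretest. The only phase contrast they offer is active implementation against maintenance. In the active phase the series is built on few patients at first and many later. If the number then holds up in maintenance, the plot becomes steadier even when nothing about the patients has changed. A reader following item 3 could take this as a stabilising effect of the phase. Weekly substance use is one of these series.

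The comparison across clinics has a related weakness. The sites were chosen to differ and include "a relatively small, rural, freestanding FQHC with integrated behavioral health services". Where the numbers behind a series differ between clinics, raw scatter differs for that reason alone.

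**Working it through.** The plan gives no figure on this point to reproduce. The check asks how large a scatter change enrolment alone could produce.

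**Inputs from the document.** Recruitment lasts 12 months (Timeline), with at most 100 Seva patients per clinic (Reach). The six-month follow-up of effectiveness measures and Seva use is in Table 1 and the Maintenance section.

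**Assumptions (not in the document).** Patient-level SD is 1. Enrolment is linear to the full 100, everyone reports, and one point is plotted per month. The process SD, tau, runs from 0 to 0.3 patient SD. Maintenance n is 100, or falls.

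**Formula.** SD of a monthly clinic mean = sqrt(tau² + 1/n). Ratio of active to maintenance SD = sqrt[(tau² + mean(1/n_k)) / (tau² + 1/100)].

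**Step 1: the enrolment build-up.** n_k = 100k/12, rounded: 8, 17, 25, 33, 42, 50, 58, 67, 75, 83, 92, 100. Then mean(1/n_k) = 0.0314, against 1/100 = 0.0100. With tau = 0 the ratio is sqrt(0.0314/0.0100) = 1.77. (Without rounding, mean(1/n_k) = 0.0310 and the ratio is 1.76.) If maintenance n is 50, the unrounded ratio is sqrt(0.0310/0.0200) = 1.25.

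**Step 2: adding process variation.** The second column is the formula above. The last two columns are simulated: the chance that a two-sided 5% F-test on detrended monthly values calls a variance difference when there is none beyond n. The plan proposes no such test; it serves here only as a yardstick.

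| tau (patient SD) | SD ratio | 12 vs 18 months at n = 100 | 12 vs 6 months at n = 100 |
|---|---|---|---|
| 0 | 1.77 | 45% | 16% |
| 0.05 | 1.65 | 37% | 13% |
| 0.1 | 1.44 | 23% | 9% |
| 0.2 | 1.20 | 10% | 6% |
| 0.3 | 1.10 | 7% | 5% |

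With tau = 0 and reporters falling from 100 to 40 in maintenance, the rates are 23% (18 months) and 9% (6 months).

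**Step 3: a simpler yardstick for the eye.** Take an observed SD ratio of at least 1.5, earlier over later phase, with 12 points in each phase and tau = 0. At equal n this occurs by chance 9.7% of the time. With the enrolment build-up followed by n = 100 it occurs in 64%, and followed by n = 50 in 27%.

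**Step 4: stable denominators.** With n = 200 in both phases the ratio is 1.00 and the chance stays at 9.7%. With n going from 200 to 240 and tau = 0 the ratio is sqrt(240/200) = 1.10 and the chance is 16%. The problem needs roughly a two-fold change in n, with scatter that is mainly sampling error.

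**Step 5: the obvious correction.** Multiplying each deviation by sqrt(n) brings the rate back to about 5% at tau = 0. At tau = 0.2 with 18 months it over-corrects: about 11 to 12%, against 10% for the raw values. Limits therefore need a between-month component as well.

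**The case against.** A reader might infer that the plan counts a variability shift as an effect in its own right, and that this criterion will be met with no change in performance. The document does not support that. Item 3 sets no rule or threshold; variability is one of three features read together, beside a regression that already weights for the counts. This part of the objection stands, and the point is about what can happen.

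A reader might also infer that every plotted series is affected. It is not. Electronic health record series run for 48 months on clinic aggregates, and nothing shows that their denominators follow Seva enrolment. Staff surveys cover listed staff. The patient survey has four waves, not a monthly build-up. Each clinic is its own pretest control, so a stable clinic size cannot create a phase shift within that clinic. The size argument bears only on raw comparisons across clinics, and no clinic counts are given to put a figure on it.

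The large figures are a favourable case for the concern. They assume zero process variation, full enrolment and complete reporting. With six maintenance months and a process SD of 0.1 to 0.2, the yardstick test falls to 9% to 6%, close to nominal. Maintenance n is not fixed either, since sites may keep recruiting and some users may drop out. Item 3 covers selected outcomes and does not say that Seva series are among them.

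Finally, chart conventions may sit in a fuller document. That is fair for the choice of chart. It does not remove the mismatch in the text shown, which gives an allowance for the counts in item 2 and states a causal reading of variability in item 3 without one.

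**Conclusion.** The concern holds in a limited form. For Seva check-in and log series, a fall in scatter from active phase to maintenance can be produced by enrolment alone, and item 3 gives the reader nothing with which to tell this from a real change. Under linear enrolment to 100, complete reporting and no process variation, the SD ratio is about 1.8. It is 1.4 at a process SD of 0.1 patient SD and 1.2 at 0.2, and tends to 1 beyond that. Enrolment path, patient SD and process SD are all assumptions. Within a clinic, record-based and staff series with a stable denominator are not affected. Level and trend readings are not called into question here. This is an interpretive weakness in a supplementary descriptive analysis, worth correcting because it can reach weekly substance use and the correction is cheap.

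**What to change.** Add to item 3:

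1. Show the number of patients or staff with each plotted point.
2. For series that start at enrolment (Seva check-ins and log data), do not treat a change in raw variability as evidence of an effect.
3. Do not compare raw variability across clinics of different size.
4. Where variability is read, read it against limits that use the n at each point and also include a between-month variance component, not pure sqrt(n) scaling.

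The counts are already needed for the item 2 weights, so the work is a little plotting code and a few sentences. The price is that variability is no longer usable as evidence for a few series.
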